#### Capability Set for Work Questionnaire (CSWQ)

The CSWQ is a valid instrument to measure work capabilities (Abma et al., 2016). The questionnaire explores whether a set of seven valued work aspects, are considered valuable by the worker (A), are enabled in the work context (B), and can be achieved (C). In relation to each of these seven valued work aspects the worker is asked (A) 'How important is <the value> for you?' (B) 'Does your work offer the opportunities to achieve <the value>' and (C) 'To what extent do you actually achieve <the value>?' on a scale from 0 = 'definitely not' to 5 = 'very much'. An individual value is considered part of the capability set of an individual worker when it is considered important (A) (score 4–5), and the workplace offers the opportunity to achieve the value (B) (score 4–5), and the worker is able to achieve the value (C) (score 4–5). The capability set can therefore encompass up to seven values. The combined score of all items results in a total score for the capability set. An overall question for the capability for work was posed: 'Taking all things together, I think I have enough opportunities to remain working', which required a response ranging from 1 = 'totally disagree' to 5 = 'totally agree' (van Gorp et al., 2018).

The CSWQ will only be administered in patients that are employed (including self-employed patients). It is not applicable for persons that are not employed.

### **6.1.3 Other study parameters**

A number of qualitative measures will be used for the following research objectives:

- To develop rehabilitation care for patients with NMD that is based on the capability approach (a more detailed description can be found in chapter 5.1.2)
- To assess treatment fidelity in designing capability care, training of the health care professionals in providing capability care, delivery of capability care, and receipt and enactment of capability care by the patients with NMD.
- To determine how capability care, in comparison to usual care, facilitates changes in resources and conversion factors, enlarging functionings and capabilities.

Relating this to the MRC framework for process evaluation (Moore et al., 2014, 2015), the first objective relates to the development of the intervention, the second objective refers to the implementation process, whereas the third objective relates to both the mechanisms of impact and to the context.

We will use a selection of commonly used quantitative and qualitative methods listed by the MRC for process evaluation (Moore et al., 2014), such as non-participant observations, analysis of routine data, self-report questionnaires, one-to-one interviews and focus groups. This data will be collected through:

- Consultations with the health care professionals
- Multidisciplinary team meetings
- Medical reports
- Questionnaire on resources and personal characteristics
- Interview on experiences with provided care (with patients and if possible their partners)
- Focus groups with health care professionals

#### Consultations with the health care professionals

Audio recordings of the consultations (in usual care and capability care) with the health care professionals will be made. These recordings will be used to evaluate the delivery of capability care (an aspect of treatment fidelity) and in what respect capability care differs from usual care. They will be analysed in terms of the capability approach and based on the seven capability dimensions used by Alkire (2002). These dimensions are: (1) Life, health; (2) Knowledge; (3) Aesthetic experience; (4) Play; (5) Sociability (friendship); (6) Practical reasonableness; (7) Religion or transcendence. The analysis is described in more detail in paragraph 8.3.

#### Multidisciplinary team meetings

Audio recordings of the multidisciplinary team meetings (in usual care and capability care) will be made. In these team meetings, the findings of all health care professionals are discussed, which leads to a decision on how to continue the rehabilitation for each patient. These recordings will be used to evaluate the delivery of capability care (an aspect of treatment fidelity) and in what respect capability care differs from usual care. They will be analysed in terms of the capability approach and based on the seven capability dimensions used by Alkire (2002). These dimensions are: (1) Life, health; (2) Knowledge; (3) Aesthetic experience; (4) Play; (5) Sociability (friendship); (6) Practical reasonableness; (7) Religion or transcendence. The analysis is described in more detail in paragraph 8.3.

#### Medical reports

All medical reports (including reports from e.g. allied health professionals and nurses) from the departments of neurology and rehabilitation during the inclusion period of the patient will be analysed, to determine the delivery of capability care (an aspect of treatment fidelity) and in what respect capability care differs from usual care. The medical reports will be obtained from the electronic patient file (EPIC) and will be analysed in terms of the capability approach and based on the seven capability dimensions used by Alkire (2002). These dimensions are: (1) Life, health; (2) Knowledge; (3) Aesthetic experience; (4) Play; (5) Sociability (friendship); (6) Practical reasonableness; (7) Religion or transcendence. The analysis is described in more detail in paragraph 8.3.

#### Questionnaire on resources and personal characteristics (self-developed)

A short questionnaire has been developed (see appendix F) to determine resources at patients' disposal (e.g. income, formal and informal care and the use of aids). This

information will be analysed quantitatively (to describe the patient group) and qualitatively (to triangulate with the results from the interviews). In capability terminology, the information from these questionnaires will provide insight into resources.

#### Interview on experiences with provided care (at follow-up)

At follow-up, a retrospective interview with the patients and if possible with their partners will be conducted.

This interview focuses on how the patients (and their partners) have experienced the health care and how this has changed several aspects in their lives, and on the limitations and barriers that prevent making these changes (see interview guide in appendix F; outcome measures). If partners are willing to participate in the interview, a separate interview with the partner will be conducted (see interview guide in appendix F). Interviews will be audio-recorded.

Interviews will be held and analysed in parallel until data saturation has been reached. This point is reached when the experiences do not provide new insights. When collecting and analysing in parallel, this ensures that emerging themes from earlier interviews can be investigated in more depth in later interviews (Moore et al., 2014). It is expected that per group (usual and capability care groups), between 10 and 20 patients and if possible their partners will be interviewed.

#### Focus groups with health care professionals

After the capability care group has completed their rehabilitation treatment, focus groups will be organised with the health care professionals to discuss their experiences with delivering capability care. Depending on the exact number of health care professionals involved in the study, we will organise around 5 focus groups with 4-6 health care professionals per group. The topics introduced during the focus groups by the research team are: the capability care training, the delivery of capability care during rehabilitation treatment of different patients, the receipt of capability care by the patients, the contextual factors involved that enable or prohibit the delivery of capability care, and the differences with usual care. Focus group sessions will be audio-recorded.

### 6.3 Study procedures

All subjects will undergo the measurements as listed in the tables below (table 2 and 3) during the baseline measurement (T0) and 6 months after the baseline measurement (T1). Subjects in both groups (usual care and capability care) will undergo the same assessment procedure. For all questionnaires, the preferred method of assessment is online. The cloud-based clinical data platform CastorEDC will be used for this. Participants will receive an invitation with an online link in their email. If a participant prefers administration with pen and paper, this is also possible. In that case, questionnaires will be sent by post.

There are two exceptions when participants will not undergo all assessments:

- The CSWQ will only be administered when a participant is employed, including self-employment.
- The interview on the patient's experience with the provided health care is expected to be conducted with 10-20 participants per group and if possible their partners.

The COPM is a semi-structured interview that will be conducted by research assistants. These assistants are experienced occupational therapists that are familiar with using the COPM. The interview will be conducted by phone or a video call.

The interviews on experiences with provided care will be conducted by researchers or research assistants. An interview guide (appendix F) will be used. Furthermore, researchers and research assistants will discuss their experiences with conducting the interviews. Analysis of the audio recordings of interviews will be conducted by an independent researcher (someone that has not conducted the particular interview).

Table 2. Overview of baseline measurements.

| T0: Outcome measure                                     | Method of assessment      | Duration     | Assessor           |
|---------------------------------------------------------|---------------------------|--------------|--------------------|
| COPM                                                    | Semi-structured interview | 60 minutes   | Research assistant |
| ICECAP-A                                                | Questionnaire             | 5 minutes    | Online by patient  |
| USER-P                                                  | Questionnaire             | 10 minutes   | Online by patient  |
| EQ-5D-5L                                                | Questionnaire             | 5-10 minutes | Online by patient  |
| SF-36                                                   | Questionnaire             | 10 minutes   | Online by patient  |
| CSWQ                                                    | Questionnaire             | 10 minutes   | Online by patient  |
| Questionnaire on resources and personal characteristics | Questionnaire             | 5-10 minutes | Online by patient  |

Table 3. Overview of follow-up measurements.

| T1: Outcome measure                                     | Method of assessment      | Duration                                             | Assessor                                  |
|---------------------------------------------------------|---------------------------|------------------------------------------------------|-------------------------------------------|
| COPM – re-scoring                                       | Semi-structured interview | 5 minutes                                            | Research assistant                        |
| Interview on experiences with provided care             | Semi-structured interview | 55 minutes (and if possible 55 minutes with partner) | Researcher (BB, EP) or research assistant |
| ICECAP-A                                                | Questionnaire             | 5 minutes                                            | Online by patient                         |
| USER-P                                                  | Questionnaire             | 10 minutes                                           | Online by patient                         |
| EQ-5D-5L                                                | Questionnaire             | 5-10 minutes                                         | Online by patient                         |
| SF-36                                                   | Questionnaire             | 10 minutes                                           | Online by patient                         |
| CSWQ                                                    | Questionnaire             | 10 minutes                                           | Online by patient                         |
| Questionnaire on resources and personal characteristics | Questionnaire             | 5-10 minutes                                         | Online by patient                         |

## 6.4 Withdrawal of individual subjects

Subjects can leave the study at any time for any reason if they wish to do so without any consequences. The investigator can decide to withdraw a subject from the study for urgent medical reasons.

### 6.4.1 Specific criteria for withdrawal

Not applicable.

## 6.5 Replacement of individual subjects after withdrawal

When a subject withdraws from the study, it will not be replaced. With an inclusion of 30 subjects per group, if a maximum of 6 participants per group withdraw, the expected effect of

the intervention will still show a significant effect (see power calculation as described in chapter 4.4).

### **6.6 Follow-up of subjects withdrawn from treatment**

Subjects that withdraw from the study will be forwarded for aftercare to their general practitioner, neurologist or rehabilitation physician if needed. Depending on the participant's need, referral to the right health care provider will be arranged. Subjects can also withdraw from the study without terminating their multidisciplinary treatment. In that case, the health care providers will be notified of the subject's withdrawal.

The data collected from subjects that have withdrawn from the study will not be used, as this will only consist of baseline measurements when a subject has withdrawn. With the present study design, consisting of only two measurement moments, it is not possible to use an intention-to-treat analysis for the subjects that have withdrawn. However, the number of withdrawals and reason for withdrawal (if the patient is prepared to share his reason) will be described. With the collected baseline-data and reasons for withdrawal, we will analyse whether there is a certain pattern to be found for patients withdrawing from the study.

### **6.7 Premature termination of the study**

In case of any unforeseen, premature termination of the study, all participants will be informed by the researcher. Participants can indicate if they agree on storage of the data obtained until that point.

## 7. SAFETY REPORTING

### 7.1 Temporary halt for reasons of subject safety

In accordance to section 10, subsection 4, of the WMO, the sponsor will suspend the study if there is sufficient ground that continuation of the study will jeopardise subject health or safety. The sponsor will notify the accredited METC without undue delay of a temporary halt including the reason for such an action. The study will be suspended pending a further positive decision by the accredited METC. The investigator will take care that all subjects are kept informed.

### 7.2 AEs, SAEs and SUSARs

#### 7.2.1 Adverse events (AEs)

Adverse events are defined as any undesirable experience occurring to a subject during the study, whether or not considered related to the experimental intervention. All adverse events reported spontaneously by the subject or observed by the investigator or his staff will be recorded.

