### 3. STUDY DESIGN

Two patient groups are included in a controlled before and after design. The first group of 30 patients will be included during a period of 6 months; they will be provided with optimal care as usual, and followed up for a period of 6 months after inclusion. The data from this group will be used to develop and design the intervention (capability care), as described in more detail in chapter 5.1. Then, during a period of 3 months, members of the multidisciplinary outpatient rehabilitation care team at Radboudumc will be trained in providing capability care. Subsequently, the second group of 30 patients will be included during a period of 6 months; they will be provided with capability care, and followed up for a period of 6 months after inclusion.

The baseline measurements will take place before the appointments with the health care professionals at the department of rehabilitation. The baseline measurements include an interview for the COPM (by an independent research assistant) and a number of questionnaires that patients can digitally fill out from home (online) without supervision.

The follow-up measurements will take place 6 months after the baseline measurements. Patients will be asked to fill out the same questionnaires as in the baseline measurement. Additionally, an interview will be conducted in which the COPM is re-scored and patients (and if possible their partners) are asked on how they experienced the healthcare provision. COPM re-scoring will be done by an independent research assistant; interviews will be conducted by both the researchers and research assistants.

Patients in both the usual care group and capability care group will undergo the same measurements. All study assessments not completed will be documented as missing data.

The study design is illustrated in the flowchart below (fig. 2).

[figure not shown]

Figure 2. Flowchart of the study design.

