### **9.3 Benefits and risks assessment, group relatedness**

The participants in the intervention group receive healthcare based on the capability approach (capability care). It is expected that this type of healthcare is more person-centred and will lead to a higher quality of life for patients with neuromuscular disease. The provision of rehabilitation care with an explicit focus on strengthening patients' capabilities is not expected to incur greater risk than treatment as usual.

Participants in both the usual care and capability care groups undergo two measurement moments. Measurement moments contain an interview (1 hour) and self-report questionnaires (electronically or on paper) (50 minutes). The interview will take place at the Radboudumc or at a location convenient for the participant (at home) so that travel time is limited. The measurements are non-invasive and no health risks are expected. Participants possibly are confronted with their limitations by the questionnaires or during the interviews. The research assistants are trained occupational therapists who can address concerns of participants or advise participants to visit other health professionals.

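### Adverse events are captured only if volunteered or observed, and follow-up contact is uneven; one identical question to every patient at T1 would be a cheap improvement

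*Protocol*

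**What the plan says.** Section 7.2.1 defines harms broadly: "Adverse events are defined as any undesirable experience occurring to a subject during the study, whether or not considered related to the experimental intervention". The collection rule is narrower: "All adverse events reported spontaneously by the subject or observed by the investigator or his staff will be recorded". Neither the baseline schedule (Table 2) nor the follow-up schedule (Table 3) contains an adverse event item.

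The Summary and section 9.3 name one participant risk: "Participants possibly are confronted with their limitations by the questionnaires or during the interviews". The support offered is that "The research assistants are trained occupational therapists who can address concerns of participants or advise participants to visit other health professionals". Section 3 describes the baseline questionnaires as "a number of questionnaires that patients can digitally fill out from home (online) without supervision", and Tables 2 and 3 list every questionnaire as completed online by the patient.

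For follow-up, section 6.3 says: "The interview on the patient's experience with the provided health care is expected to be conducted with 10-20 participants per group". Section 6.1.3 gives the stopping rule: "Interviews will be held and analysed in parallel until data saturation has been reached". Table 3 allots 55 minutes to this interview, held by a researcher or a research assistant, and 5 minutes to the COPM re-score, which every patient is due to have. Section 3 adds that "COPM re-scoring will be done by an independent research assistant".

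**The concern.** A broad definition combined with passive collection tends to record what patients happen to mention. How much they mention plausibly depends on how long they talk with study staff, and at T1 that varies from 5 minutes to about an hour. Because saturation decides how many have the long interview, the mix of short and long contacts can differ between usual care and capability care. The groups are also treated in successive periods by a team that knows which care it gives, so events noted by staff are not an even-handed check.

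There is a related gap in the support for the named risk. That risk includes the questionnaires, but the people meant to help are not present when the questionnaires are completed at home.

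At stake is whether the study's account of harms is reasonably complete and comparable between groups. The efficacy comparison is not at stake.

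**Working it through.** The protocol states no figure for adverse event capture, so there is none to reproduce. The check is of scheduled contact, followed by an illustration.

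**Scheduled contact with study staff**

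| Moment | Who | Contact | Adverse event question written? |
|---|---|---|---|
| T0 (Table 2) | all | COPM interview, 60 minutes, research assistant | no |
| T1 (Table 3) | all | COPM re-score, 5 minutes, research assistant | no |
| T1 (Table 3, section 6.3) | 10 to 20 per group | care-experience interview, 55 minutes, researcher or research assistant | no |

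Section 5.1.1 adds clinical contacts for all patients: the consultations on the appointment day, a closing talk with the rehabilitation physician or physician assistant, and contact from the rehabilitation physician after 3 months. No adverse event question is attached to these either, though events can be volunteered or observed there.

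**Share without the long interview.** With 30 per group (section 4.4):

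- 20 interviewed: (30 − 20)/30 = 10/30 = 33% not interviewed.
- 10 interviewed: (30 − 10)/30 = 20/30 = 67% not interviewed.

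**An inconsistency behind these shares.** The Summary and section 9.3 describe a one-hour interview at both measurement moments. At T1 this matches Table 3 only for interviewed patients: 5 + 55 = 60 minutes. For the rest, sections 6.1.3 and 6.3 leave 5 minutes. The 33% to 67% follows sections 6.1.3 and 6.3 and is certain only once these passages are reconciled.

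**Illustration of unequal capture.** Let k be the number interviewed out of 30, a the chance that an event is recorded in an interviewed patient, and b the chance in another patient. Group capture is [k·a + (30 − k)·b]/30. The protocol gives neither a nor b. I assume a = 0.80, vary b, and compare the two ends of the expected range, k = 10 and k = 20.

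| b | k = 10 | k = 20 | Ratio of recorded events at equal true rates |
|---|---|---|---|
| 0.80 | (8 + 16)/30 = 0.80 | (16 + 8)/30 = 0.80 | 1.00 |
| 0.50 | (8 + 10)/30 = 0.60 | (16 + 5)/30 = 0.70 | 1.17 |
| 0.30 | (8 + 6)/30 = 0.47 | (16 + 3)/30 = 0.63 | 1.36 |

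The ratio is 1.00 whenever the interview makes no difference to reporting, and also whenever both groups have the same number of interviews. It exceeds 1 only if both differ, and the table uses the largest imbalance within the expected range.

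**The case against.** The best defence is proportionality. Section 10.2 puts the study in the negligible-risk class. Section 5.1.2 keeps the number of consultations and tests the same in both pathways and changes the content of the conversations. Adverse events are not an endpoint, and no between-group analysis of them appears in Tables 4 and 5 or in sections 8.1 and 8.2. Passive recording can be a reasonable choice here. All of this stands, and it limits the weight of the point.

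It also stands that capture is wider than spontaneous report. Staff observation counts, every patient has the T0 interview and the clinical contacts above, and the research team reads neurology and rehabilitation reports for the inclusion period (section 6.1.3).

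A reader might infer more than the protocol supports:

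- *That harms will be missed, or that the named risk cannot be detected.* The documents show neither. That risk also covers the interviews, and every patient speaks with a research assistant at T0 and at T1 and can raise distress then.
- *That the research assistants are the route for collecting adverse events.* Section 9.3 offers them as support for participants' concerns and does not describe a collection method.
- *That the safety comparison is biased.* No such comparison is planned, and the expectation of no greater risk in section 9.3 is a benefit-risk statement, not a hypothesis under test.
- *That much care is given elsewhere, out of the study's sight.* Section 5.1.1 lists referral to a regional centre or to primary care as possible advice and gives no proportions.

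What remains is that no scheduled contact carries a question about harms, and that the chance to volunteer them at T1 is uneven.

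**Conclusion.** The point holds as a minor one. The passive rule and the absence of any scheduled question are plain in the text. Adverse events, including distress from the home questionnaires, may be under-recorded, possibly to a different degree in the two groups. By sections 6.1.3 and 6.3, between one third and two thirds of each group have only the 5-minute re-score as scheduled T1 contact with study staff.

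The ratios of 1.00 to 1.36 show direction only. They rest on assumed capture chances and on the largest imbalance in interviews within the expected range. No efficacy result, sample size or significance level changes.

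**What to change.** In section 7.2.1, keep spontaneous and observed events and add one open question, worded identically and put to every participant in both groups at the T1 COPM contact. Ask it after the COPM has been re-scored, so that it cannot influence the primary outcome. It should cover any new health problem, any hospital admission, and any distress from the care, questionnaires or interviews since T0. Record the answers as adverse events and add the item to Table 3.

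Reconcile the one-hour interview at both moments (Summary, section 9.3) with the 10 to 20 interviews per group (sections 6.1.3 and 6.3). Align the support text in the Summary and section 9.3 with the unsupervised questionnaires and with interviews held by researchers.

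Leave the order of the T0 questionnaires and COPM interview as it is. Requiring questionnaires first could delay a baseline that must precede the appointments, and could influence which activities patients name.

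The cost is a slightly longer T1 contact and more adverse events to process, most of them probably unrelated to the care. No extra visit or staff is needed. The question will not reach patients who withdraw before T1; for them spontaneous and observed reports remain the only source.
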